## Assessment of perceptions and behavioral changes triggered by mother groups through focus groups.

Mother groups for parenting are new in Zambia, and no study has studied their dynamics. We would like to understand and document mother perceptions, behavioral changes and changes in the support network related to mother groups through a qualitative study using focus group discussions. Qualitative research allows researchers to investigate process changes and other themes that cannot be captured by the endline quantitative assessment by having participants identify channels, challenges and themes related to the mother groups, and inform future implementation of mother groups.

Focus group discussions will be conducted to determine the perceptions of the mothers on the mother’s groups, mother’s perceptions on their behavior change since attending the mother groups and their feelings of belonging, social capital and if they have established any social networks since they began attending these groups. We will conduct:

- 4 focus groups with mothers participating in the study and attending mother groups, each group with 6-9 mothers invited. Focus groups will be done at the health facility and will be approximately one hour in length. Mothers will be recruited by facility, with the exception of one focus group that will recruit mothers from two facilities. Each mother will be selected from a different mother group to maximize privacy and make the mothers more comfortable in talking about their group. For each mother group, the study ID of one mother will be randomly selected. The selected mother will be approached by the CDA; if the mother is not interested in participating, another mother will be randomly selected.
- 3 focus groups with mother heads participating in the study, each with 4-7 participants. Mother heads are study participants who volunteered to head the mother groups. Sampling will be divided in a first group including the first two facilities, a second group including the other two, and the last facility by itself because too isolated. For each sample strata, we will randomly select 6 mother groups and invite their mother head for the FGD.
- 1 focus group with CDAs (which we consider key informants) with all of the 10 CDAs.

Informed consent for focus groups. The focus groups will record age, parity, marital status, education and attendance, but this information will not be linked to facility catchment area nor to any other information collected as part of the main study. No other personal health information or personal data will be used nor collected. The focus group discussions will be minimal risk and, as a result, we will use verbal rather than written consent using a verbal script form instead of a written informed consent form.

Data collection for focus groups: All the staff involved in focus group discussions will be trained in confidentiality and research ethics. Interviews will be done in either Tonga or English, and recorded using a digital recorder. No last names nor village nor facility will be mentioned during the recorded session. Sequential IDs will be given to participants for referring to each other.

The following steps will be followed: a) explanation of information sheet and informed consent process; b) introduction; c) explanation of the process; d) logistics; e) ground rules and emphasis on confidentiality; f) collection of age, parity, marital status, education and attendance for each FGD ID; g) turn on tape recorder and conduct FGD following FGD guide; h) turn off tape recorder, thank the mother; give refreshment and transport reimbursement.

## Sample Size Calculations

The study is designed to detect increases in standardized child development scores of 0.5 standard deviations with power = 0.9. The main assumptions underlying this calculation are an average group size of 20 children in each of the 30 zones, and an intra-class correlation coefficient of 0.1 (a design effect of 2.9). Similarly, the study is powered to detect an increase in height-for-age z-scores of 0.5 standard deviations in the intervention arm relative to the control arm. We aim to enroll 250 children in each study arm for a total sample of 500 children. In order to account for lost to follow-up, we aim to recruit up to 5% additional children per study arm (262 per arm).

For the year two follow-up assessment, we are powered to detect an increase in standardized child development scores, as measured by the BSID-III, of 0.3 standard deviations with power 0.8.

Sample size for health facility surveys and feeding centers is seven. There will be 10 health workers interviewed (assuming 2 per health facility), 5 national, provincial and district level nutritionists or clinical-care specialists and the feeding sample size for assessment of dietary intake will be all willing and enrolled intervention children (estimate 275).

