## Specific objectives

**Specific objective #1:** To conduct a cluster-randomized controlled trial to determine whether a community-based package of interventions targeted at early childhood development (ECD) and delivered by community development agents (CDAs) can reduce stunting and improve cognitive and motor development by two years of age.

The study will have two primary outcomes:

1. **Prevalence of stunting (height-for-age z-score (HAZ) < -2) at age 2.**
2. **Cognitive and motor development by age 2 years as measured with a standardized test developed as part of the multinational INTERGROWTH-21^st^ study** [[13](#_ENREF_13)]. The assessment tool combines elements of four existing testing instruments (Bayley Scales of Infant Development (BSID), the Rapid Neurodevelopment Assessment (RNDA), the Malawi Development Assessment Tool and the Griffith’s Scales) and simultaneously assesses cognition, language, motor skills and behavior.

**Specific objective #2:** To determine whether the intervention improves effective access to child health services. This will be measured by the following secondary outcomes:

- Vaccination rates
- Vitamin A supplementation
- Utilization of routine child health check-up services

**Specific objective #3:** To determine whether the intervention alters caregiver interactions with children. We will use the *Home Observation for Measurement of the Environment* (HOME) inventory [[14](#_ENREF_14)]. This will be measured by the following secondary outcomes:

- Availability of books, toys and other reading materials at home
- Time spent by caregivers reading to the child
- Time spent by caregivers playing with the child

**Specific objective #4:** To determine whether there are secondary benefits of mother/caregiver-led-support groups in terms of maternal mental health. This will be measured by the following secondary outcomes:

- Maternal depression, captured with the SRQ-20 questionnaire, a test validated internationally including in neighboring Malawi[[15](#_ENREF_15)]

**Specific objective #5:** To determine the types and quality of nutrition services currently provided in the five health centers and referral feeding centers. This will be collected via a structured KII with nutritionist or clinical care specialists at the national, provincial and district levels. Questions will focus on:

- Current policies and guidelines relating to child health and nutrition

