### 3.1.2 Internal validity

Power calculations indicate that the selected number of health zones will be sufficient to detect the expected impact on our primary outcomes. After randomization, the soundness of the randomization as a procedure to control for confounding will be checked by comparing variables obtained through the baseline survey and through community level data. Examples of baseline variables that will be compared are maternal age, education and occupation; child age and gender; birth weight of the child; duration of breastfeeding length; and initial vaccination status. We will also include community level baseline variables such as distance to health center and District Medical Office, road access and presence of community health workers. Although blinding of treatment will not be possible due to the very nature of the intervention, we do not expect Hawthorne effects to be significant in this case due to the length of the program. We also do not foresee important concerns due to differential attrition in the two arms because of the long-standing relationship of ZCAHRD in all of these communities (both the control and intervention) established through the previous ZamCAT study.

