# Data analysis

We will use the following primary outcomes:

1. Proportion of children with stunting (height-for-age Z-score less than 2 standard deviations below the mean);
2. Child development scores using the INTERGROWTH tool;

Other outcomes of interest include:

1. Proportion of children receiving all age-appropriate vaccines
2. Proportion of children receiving vitamin A supplementation;
3. Number of well-baby visits attended;
4. HOME score;
5. Average time spent reading with the child;
6. Average time spent playing with the child;
7. Proportion of women scoring as depressed, based on the SRQ-20.

We will investigate the relative risk associated with random group assignment as a fixed covariate predicting each outcome using generalized estimating equations (GEE) models that take into account the clustering by health facility. We will use an exchangeable correlation structure in the model.

We will compare baseline characteristics between the two groups that may be related to the outcome, but we expect randomization to have created reasonably balanced groups. Categorical variables will be compared between groups using the chi-square test or Fisher’s exact test if cell sizes are small, continuous variables using t-tests if normally distributed or non-parametric Wilcoxon rank sum tests, if non-normal. We will adjust for confounders as appropriate.

Potential confounders include: maternal education, paternal education, socio-economic status, baseline nutritional status, and presence of food insecurity. The process of randomization should help to balance confounders across the two study arms. Crude and adjusted risk ratios will be presented with 95% confidence intervals in appropriate tables.

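### The growth primary outcome is stunting prevalence, but the sample size section powers only a difference in mean height-for-age z-score, so the claim of sufficiency is unsupported for stunting

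*Protocol*

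**What the plan says.** Under Specific objectives, the first of the two primary outcomes is "Prevalence of stunting (height-for-age z-score (HAZ) < -2) at age 2". The Data analysis section repeats it as "Proportion of children with stunting (height-for-age Z-score less than 2 standard deviations below the mean", and the analysis for Objective 10 uses the same definition at the year-two follow-up. The model is described on a ratio scale: "We will investigate the relative risk associated with random group assignment as a fixed covariate predicting each outcome". Mean HAZ appears in none of the outcome lists.

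The Sample Size Calculations section first sets the target for the development score, to "detect increases in standardized child development scores of 0.5 standard deviations with power = 0.9". It assumes "an average group size of 20 children in each of the 30 zones" and an ICC of 0.1, giving a design effect of 2.9. For growth it then says: "Similarly, the study is powered to detect an increase in height-for-age z-scores of 0.5 standard deviations in the intervention arm". The power is not repeated there. The opening word carries over 0.9 and, by implication, the ICC. The enrolment target is 250 per arm, or 262 with the allowance for loss to follow-up. The year-two power statement covers only the BSID-III.

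Section 3.1.2 concludes: "Power calculations indicate that the selected number of health zones will be sufficient to detect the expected impact on our primary outcomes".

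**The concern.** A 0.5 SD shift in a continuous score and the change in the proportion below a cut-off that this shift produces are not equally easy to detect. Dichotomising discards information, so a sample that gives 90% power for the mean gives less for the proportion. The protocol sizes the first and tests the second. A reader who takes section 3.1.2 together with the sample size section would believe that the stunting comparison has about 90% power, and might give a null result more weight than the design can bear.

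This is not detail left to a statistical analysis plan. The protocol contains both the sample size calculation and the sufficiency claim, and for growth they address a different quantity from the one it names as primary.

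**Working it through.** **Inputs from the protocol.** 0.5 SD effect, ICC 0.1, 20 children per zone, 30 zones (15 per arm), design effect 1 + 19 × 0.1 = 2.9, 250 children per arm (Sample Size Calculations; Determination of clusters and randomization). Stunting of 36% among under-5s in Southern Province (Summary).

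**Assumptions not in the protocol.** Two-sided alpha 0.05; 36% as the control rate at endline; normal HAZ, shifted by 0.5 SD with unchanged spread.

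**Step 1: reproduce the stated power for a mean.** n per arm = 2 × (1.960 + 1.282)² / 0.5² = 84.1, rounded up to 85. Then 85 × 2.9 = 246.5, against the stated 250. Conversely, effective n = 250 / 2.9 = 86.2, and power = Φ(0.5 × √(86.2/2) − 1.96) = 0.907. The stated 0.90 is reproduced.

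**Step 2: translate the same shift into stunting.** The 36% point of the normal distribution is −0.358. After the shift it is −0.858, and Φ(−0.858) = 0.195. The contrast is 36% versus 19.5%, a difference of 0.165.

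**Step 3: cluster sizes.** The protocol's figures do not fit together exactly: 15 zones of 20 make 300 per arm, while 250 per arm in 15 zones make 16.7 per zone. Three readings are carried:

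| Reading | Design effect at ICC 0.1 | Effective n per arm |
|---|---|---|
| A: 250 per arm, printed design effect | 2.9 | 86.2 |
| B: 250 per arm, 16.7 per zone | 1 + 15.67 × 0.1 = 2.57 | 97.4 |
| C: 300 per arm, 20 per zone | 2.9 | 103.4 |

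**Step 4: which ICC applies to stunting.** The protocol gives none.
- If 0.1 is the ICC of stunting itself, Step 3 applies directly.
- If 0.1 is the ICC of HAZ, the normal model of Step 2 also fixes the ICC of the dichotomised outcome: [P(both of two children in a zone below the cut-off) − p²] / [p(1 − p)]. With correlation 0.1 this is 0.061 at 36% and 0.050 at 19.5%, mean about 0.056. Effective n becomes 250/2.06 = 121.5 (A), 250/1.87 = 133.5 (B) and 300/2.06 = 145.8 (C).

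**Step 5: power.** Unpooled form: Φ(0.165 / √[(0.36 × 0.64 + 0.195 × 0.805) / n_eff] − 1.96). The pooled form uses the average proportion in the null variance. Each stunting cell gives pooled to unpooled.

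| Reading | Mean HAZ, ICC 0.1 | Stunting, ICC 0.1 | Stunting, ICC 0.056 |
|---|---|---|---|
| A | 0.907 | 0.678 to 0.690 | 0.82 to 0.83 |
| B | 0.937 | 0.731 to 0.742 | 0.86 |
| C | 0.949 | 0.757 to 0.767 | 0.885 to 0.89 |

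Using each arm's own binary ICC (0.061 and 0.050) in the unpooled form gives 0.83, 0.86 and 0.89. Only if the lower value, 0.050, is applied to both arms under reading C does power touch 0.90 (0.901 to 0.907).

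**Step 6: sensitivity to the control rate (reading B, pooled).** At ICC 0.1, control rates of 30%, 40%, 45% and 50% give 0.69, 0.75, 0.77 and 0.78. At ICC 0.06 they give 0.81, 0.86, 0.87 and 0.88.

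**Step 7: detectable change.** At ICC 0.1 with 250 per arm, 90% power requires a fall from 36% to about 16% (reading B) or about 15% (reading A).

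**The case against.** The strongest objection concerns size. It is tempting to take about 74% (reading B, ICC 0.1) as the power for stunting under the protocol's own ICC. The document does not support that. The 0.1 is given for the development score and reaches HAZ only by implication; no ICC is given for a binary growth outcome. If 0.1 belongs to HAZ, the normal model that yields 19.5% also yields a binary ICC near 0.056, and power is 0.82 to 0.89. That objection stands, so the result has to be a conditional range, and a reader should not infer that power is below a conventional 80%.

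Three further points stand in part. The 36% is a provincial figure for all under-5s, not a design input; with a control rate of 45% to 50% and the lower ICC, power can reach about 0.90. The calculation is unadjusted, while the protocol foresees adjustment for baseline nutritional status and stratified randomization of zones, which could recover precision by an unknown amount. And the stated aim is feasibility and preliminary impact, which tempers how much weight a null result would be given.

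A reader might also infer an arithmetic error in the sample size section. There is none: the 0.90 for a 0.5 SD mean difference reproduces. None of these points supplies a power statement for stunting or makes mean HAZ a listed outcome.

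**Conclusion.** The mismatch stands on the text alone: the growth primary outcome is a proportion, the growth calculation is for a mean, and the sufficiency claim in section 3.1.2 has nothing behind it for stunting. The direction of the shortfall is well supported; its size is not fixed by the document. For 36% versus 19.5%, power is about 0.68 to 0.77 if ICC 0.1 applies to stunting (0.73 to 0.74 at 250 per arm, 16.7 per zone), or about 0.82 to 0.89 if 0.1 is the ICC of HAZ, against 0.91 to 0.95 for mean HAZ. With a 36% control rate and these ICCs, none of the stunting figures reaches the implied 0.90. This rests on the assumed control rate, a normal HAZ with unchanged spread, two-sided alpha 0.05 and no covariate adjustment.

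A reader might conclude that mean HAZ should become the primary outcome, since that is what was powered. The document argues against it. The section on extending the mother groups reports preliminary and first-year results, and the Time Frame puts the endline evaluation in October 2015, before the extension in April 2016. A switch now would change a primary outcome after results had been seen.

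**What to change.** 1. In Sample Size Calculations, state the power for stunting prevalence with its assumed control rate, ICC and cluster size. If ICC 0.1 is kept for stunting with 250 per arm, say that the change detectable with 90% power is about 36% to 16%. If a lower ICC is used, give it and its basis.
2. In section 3.1.2, qualify the sufficiency sentence so that it claims for stunting only what that calculation supports.
3. In Data analysis, add mean HAZ at endline, adjusted for baseline HAZ, as an additional outcome, labelled as added after year-one results. Keep stunting prevalence as the primary outcome.

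No new data are needed, since height is already measured at baseline and endline. The cost is a protocol modification, which the Ethical issues section subjects to ethics review, and a less favourable stated power for stunting.

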## Determination of clusters and randomization

Through the recent ZamCAT research efforts, the study team has established a close partnership with district health offices in six districts in Southern Province (Mazabuka, Siavonga, Monze, Choma, Kalomo and Livingstone). In total, 90 facilities were part of the recently completed ZamCAT. Since we aim for a target population of about 500 children, we will choose five facilities with approximately 100-150 children in the 6-12 months age range for the study.

From each of the five facilities, we will randomly select 50% of zones for the program, and use the remaining 50% as a control (comparison) group. The selection of zones will be based on a random number draw. We will select health facilities with six zones each for the study, which means that we expect to have 15 zones in our treatment group and 15 zones in our intervention group. We will randomize health facility zones with stratified randomization with strata based on population size and distance to the health facility; this will help ensure balance in health characteristics of the health zones and populations.

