**Extension of mother groups and follow-up assessment**

We propose to extend the mother groups component of the study to increase exposure to the parenting component of the study. Preliminary results indicated encouraging results from the mothers’ group component in terms of behavior change and engagement in the child development of their children. Mothers would like to continue the intervention and we propose

to formally support this extension. At the end of the extended period, we propose to re-assess the

cognitive and socio-emotional development of children in the intervention component. This will

allow us to measure in a more precise way and also after increased exposure to the program, both

of which will increase the power to detect a change in cognitive and socioemotional development. We will also re-assess parenting practices to observe any long-term follow-up in terms of parenting practices and engagement. The results from the first year indicate that Intergrowth might not be the best assessment tool, and we propose therefore to use the gold standard, the BSID-III.

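### The year-two power claim (0.8 for 0.3 SD on the BSID-III) states no inputs of its own, and the only planning inputs in the protocol give about 0.55

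*Protocol*

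**What the plan says.** The Sample Size Calculations section of the protocol sets the year-one target as "increases in standardized child development scores of 0.5 standard deviations with power = 0.9". For zone size and number it assumes "an average group size of 20 children in each of the 30 zones". For clustering within zones the assumption is "an intra-class correlation coefficient of 0.1 (a design effect of 2.9"). The recruitment target is "We aim to enroll 250 children in each study arm for a total sample of 500 children", raised by 5% to 262 per arm for losses. The section on determination of clusters and randomization expects "15 zones in our treatment group and 15 zones in our intervention group"; the context shows that this means 15 intervention and 15 control zones.

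A separate paragraph of the same sample size section then claims, for the year-two BSID-III assessment, an increase "of 0.3 standard deviations with power 0.8". No ICC, alpha, cluster count, sample size or covariate gain accompanies it. The section on extending the mother groups describes re-assessing children already in the study and adds no zones or children. It says that more precise measurement and longer exposure are both things "of which will increase the power to detect a change in cognitive and socioemotional development", without a figure.

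**The concern.** The year-two target effect is much smaller than the year-one effect (0.3 against 0.5 SD), yet the same children and zones are used. Required sample size varies with the inverse square of the effect, so this alone multiplies the requirement by (0.5/0.3)² = 2.8. Lowering the power from 0.9 to 0.8 recovers only part of that.

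The BSID-III score is a primary outcome at year two, and the extension is justified partly by a gain in power. If the true chance of detecting 0.3 SD is little better than one in two, the stated 0.8 would mislead anyone weighing a non-significant result.

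**Working it through.** **Inputs.** ICC 0.1, 20 children per zone, 30 zones, 250 or 262 children per arm (Sample Size Calculations); 15 zones per arm (Determination of clusters and randomization). Alpha is not stated for the power calculation. Two-sided 5% is assumed; it fits the planned 95% confidence intervals and is tested in step 1.

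**Formulas.** Design effect D = 1 + (m − 1) × ICC, with m children per zone. Effective n per arm = n / D. Power = Φ(d × √(effective n / 2) − 1.96), with d in SD units.

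**1. Year-one claim.** Power 0.9 for 0.5 SD needs 85 per arm without clustering. With D = 1 + 19 × 0.1 = 2.9, that is 85 × 2.9 = 246.5, against the stated 250. In reverse, 250 / 2.9 = 86.2 gives power 0.907. The claim reproduces. One-sided 5% gives 69 × 2.9 = 200 and does not.

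**2. Same method, 0.3 SD, ICC 0.1.**

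| Reading of the sample | D | Effective n per arm | Power |
|---|---|---|---|
| 250 per arm with the stated D | 2.9 | 86.2 | 0.504 |
| 250 per arm, m = 16.7 | 2.57 | 97.4 | 0.553 |
| 262 per arm, m = 17.5 | 2.65 | 99.0 | 0.560 |
| 300 per arm, m = 20 | 2.9 | 103.4 | 0.578 |

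A t reference with 28 degrees of freedom lowers the second and fourth rows to 0.525 and 0.549.

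**3. What 0.8 requires.** Effective n = 2 × (2.802 / 0.3)² = 174.4 per arm. At D = 2.9 that is 175 × 2.9 = 508 children per arm, about twice the plan.

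**4. Ceiling.** As m grows without limit, effective n tends to 15 / 0.1 = 150, so power tends to Φ(0.3 × √75 − 1.96) = 0.738. The ceiling is below 0.8 whenever 15 / ICC is less than 174.4, that is, for ICC above about 0.086.

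**5. ICC at which 0.8 is reached.**
- 250 per arm: D = 250 / 174.4 = 1.433, so ICC = 0.433 / 15.67 = 0.028.
- 262 per arm: D = 262 / 174.4 = 1.502, so ICC = 0.502 / 16.47 = 0.030.
- 20 per zone: D = 300 / 174.4 = 1.720, so ICC = 0.720 / 19 = 0.038.

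At ICC 0.05, power is 0.71 (250 per arm) to 0.75 (20 per zone).

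**6. Effect detectable with power 0.8 at ICC 0.1.** 2.802 × √(2 / 97.4) = 0.40 SD with 250 per arm; 2.802 × √(2 / 103.4) = 0.39 SD with 20 per zone.

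**7. Other routes to 0.8.** Ignoring clustering, 250 per arm gives 0.918. One-sided 5% gives 0.67 with 250 per arm (m = 16.7). Neither explains the stated figure.

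**The case against.** The strongest defence is that the protocol ties the ICC of 0.1 to the year-one calculation. The extension text was written with year-one results in hand, so a smaller observed ICC may lie behind the year-two figure. This stands in part. A reader might infer that the protocol asserts 0.8 at ICC 0.1 and is therefore proved false. The text does not go that far: it gives no year-two ICC, so the claim is unsupported by the stated inputs and could hold under undocumented ones.

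Three further inferences are tempting and should not be drawn:

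- *No number of children per zone could ever reach 0.8.* This is true only for ICC above about 0.086 with a two-sided 5% test. At one-sided 5% and ICC 0.1 the ceiling is 0.83, reaching 0.8 from 99 children per zone.
- *An ICC of 0.028 is the pass mark.* The threshold moves from 0.028 to 0.038 with the number of children assumed.
- *The group size and design effect must be corrected because 20 × 30 = 600, not 500.* The mismatch is real but minor. The section on clusters expects 100 to 150 children per facility in six zones, or 16.7 to 25 per zone, so 20 is within range. The design effect of 2.9 is what yields the 250 per arm, and it is conservative for year one. Changing it alters no conclusion here.

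The plan also randomizes within facility and lists adjustment covariates, which could reduce between-zone variance. No gain is quantified. It would have to cut the variance of the comparison by 41% (1 − 103.4 / 174.4) to 44% (1 − 97.4 / 174.4), and the section on data capture has the neurocognitive assessment at endline only, so there is no baseline developmental score. A more precise instrument or longer exposure may make 0.3 SD easier to achieve, but neither raises power at 0.3 SD, because the effect is already in SD units.

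Finally, the aim is feasibility and preliminary impact, and confidence intervals are planned. That softens the consequence of a null result but does not make the stated power correct.

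**Conclusion.** The year-two power statement is not supported by the protocol's own inputs. At ICC 0.1, 15 zones per arm and an assumed two-sided 5% test, power for 0.3 SD is about 0.55 (0.50 to 0.58 across the readings of the sample), against the stated 0.8; the detectable effect at 0.8 is about 0.40 SD. Those figures precede losses between the May 2014 baseline and the November 2016 evaluation. The 5% recruitment margin is the only allowance, and it is not extended for year two.

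The conclusion depends on the ICC. It would reverse at an ICC of roughly 0.03 to 0.04 or below with full retention, a value the protocol does not state. It does not depend on alpha within the usual choices: the planned sample at ICC 0.1 falls short at one-sided 5% too.

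**What to change.** In Sample Size Calculations, do one of the following:

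- Restate the year-two figure as 80% power for about 0.40 SD, equivalently about 55% power for 0.3 SD, at ICC 0.1 and two-sided 5%.
- State the year-two ICC (for example, as estimated from the year-one data), alpha, the number of children expected to be retained and any covariate gain, and show that together they give 0.8 for 0.3 SD.

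Leave the group size of 20 and the design effect of 2.9 as they are. The cost is wording only: no extra children or zones are needed, though under the first option the stated figure becomes less favourable.
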